### Data management

The database will be established by EpiData version (Atlanta, Georgia, USA) based on the CRFs project. Relevant original information will be extracted independently by the researchers. The study data will be monitored by researchers at the School of Public Health of Xiamen University every 3 months.

### Data analysis

Normally distributed continuous variables are expressed as mean ± SD and performed with paired or unpaired Student's *t*-test. Non-normally distributed continuous variables are recorded as median with interquartile range (IQR) and determined by Wilcoxon signed-rank test or Mann-Whitney *U* test. Categorical variables are presented as frequency and percentage (*N*, %) and evaluated by χ^2^ test or Fisher's exact test as appropriate. Kaplan-Meier analysis are used to calculate the mean survival time of the patients. An interim analysis is added during the trial. Both the intention to treat (ITT) principle and the per protocol (PP) analyses will be presented in our study. *P* < 0.05 (two-sided) is considered to be statistically significant. Statistical analysis will be conducted using SPSS 25.0 statistical software (IBM, Chicago, IL, USA).

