Exercise-based cardiac rehabilitation (CR) is a systematic, multidisciplinary approach to secondary prevention of cardiovascular diseases (8, 9). Exercise-based CR after acute MI is an integral component of care with Class I recommendation in American and European guidelines based on clinical and cost-effectiveness (10–12). Previous studies showed a positive prognostic value of CR in patients after MI (13, 14). A previous meta-analysis of 34 randomized trials has suggested that exercise-based CR was associated with reduced mortality and recurrent MI (15). However, it remains unclear whether patients with LVA formation after anterior MI could benefit from CR treatment. The change of peak oxygen uptake (peak VO_2_), the most well-established variable of cardiopulmonary exercise testing (CPET), will be measured as one of the primary outcomes before and after CR program in patients with LVA post-MI (16). Another primary outcome in this study is the health-related quality of life (HRQoL) measured by the EuroQol 5-Dimension-3 Level (EQ-5D-3L) after CR program and 1-year (17). This trial will also evaluate the effect of exercise-based CR on the change of cardiac function and the occurrence of major adverse cardiac cerebrovascular events (MACCE), a composite of cardiovascular mortality, non-fatal MI, non-fatal stroke, malignant arrhythmia or hospitalization for heart failure as the secondary outcomes during the follow-up period.

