## Methods

### Study design

This is a single-center, prospective, randomized controlled, single-blind clinical trial. A total of 100 participants with LVA after acute anterior MI for at least 2 months will be enrolled from 1 May 2022 to 1 May 2024 and randomized (1:1) to the CR group or control group, receiving standard drug treatment and routine health education according to the guidelines. The diagnose of LVA depends on the transthoracic echocardiography. LVA was defined as a demarcated bulge of the contour of the left ventricular wall during both diastole and systole, which showed akinesia and dyskinesia (18). In cases with suboptimal acoustic window, contrast echocardiography will be used. All of the participants will undergo percutaneous coronary intervention (PCI) before enrollment.

Participants in the CR group will receive physician-supervised home-based CR intervention. The CR program will be continued for 36 sessions. All of the participants will be followed up for 1-year. Cardiopulmonary exercise testing (CPET), transthoracic echocardiography and dynamic single-photon emission computed tomography (D-SPECT) will be performed before and after intervention. The incidence of MACCE will be recorded in the follow-up period according to the study protocol outlined in Figure 1.

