### Outcomes

The primary outcome of this study is peak VO_2_ after CR program since no definitive evidence of the impact of CR on peak VO_2_ in post-MI patients with LVA has been found so far. One of the secondary outcomes of this study is HRQoL at after CR program and 1-year quantified with the EQ-5D-3L index scores, which comprises five dimensions including mobility, self-care, usual activities, pain/discomfort, and anxiety/depression. Each dimension of the EQ-5D-3L has three levels: no problems, some problems, and severe problems, resulting in 243 kinds of different health states (23, 24). Other secondary outcomes of this study include the change of cardiac function after CR program and 1-year and the occurrence of MACCE at 1-year.

In addition, other indicators of CPET such as VO_2max_, anaerobic threshold (AT), VO_2/_HR, VO_2_/kg, carbon dioxide production (VCO_2_), ventilatory equivalent (VE), VE/VO_2_, VE/CO_2_, VE/CO_2_ slope, Metabolic equivalents (METs), HR reserve (HRR), HR_max_, VO_2_/HR, BP, ΔVO_2_/ΔWR, respiratory quotient (RQ), breathing reserve (BR), tidal volume (VT), VT/inspiratory capacity (IC), dead space volume (VD)/VT, arterial partial pressure of oxygen (PaO_2_), P (A-a) O_2_, PaCO_2_, end-tidal partial pressure of CO_2_ (PET CO_2_) and P (a-ET) CO_2_ will be obtained before and after CR program.

The cardiac function indicators by transthoracic echocardiogram and D-SPECT are as follows: LV end diastolic volume (LVEDV), LV end systolic volume (LVESV), LV end diastolic dimension (LVEDD), LV ejection fraction (LVEF), interventricular septum (IVST). In transthoracic echocardiography, LVEF was estimated using the biplane modified Simpson's method (18). Myocardial perfusion will be evaluated by D-SPECT and the following indicators will be studied: summed thickening score (STS), summed motion score (SMS), summed stress score (SSS), summed rest score (SRS), summed difference score (SDS), total perfusion defect (TPD), summed thickening score (STS), and hibernating myocardium (HM). Additionally, soluble source of tumorigenicity 2 (sST2), a myocardial fibrosis biomarker, will be detected before and after CR program as exploratory outcome (25). The outcomes will be ascertained independently and blindly by Clinical Events Committee. A diagram timeline of the study is presented in Table 1.

**Table 1 T1:** The study timeline.

	**Baseline**	**After CR program**	**At 12 months**
Demographics	X		
Medication	X	X	X
Physical examination	X	X	X

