Peak VO_2_, the highest value of oxygen uptake obtained during the exercise, is used to estimate the cardiorespiratory fitness (27). The benefits of CR are mediated mainly by improving cardiorespiratory fitness. Previous study showed that each increase of 1 ml·kg^−1^·min^−1^ in Peak VO_2_ was associated with a 15% decrease in mortality (28). Peak VO_2_ is considered to be an independent predictor for long-term survival in patients with coronary artery disease (29). The GRACE study directly targets the change of peak VO_2_ before and after personalized moderate intensity CR program and we hypothesize that the exercise training will significantly increase peak VO_2_ in participants with LVA after MI. HRQoL is becoming an important outcome measure in MI due to the high mortality and morbidity rates from MI. The potential benefits of CR post-MI on HRQoL has been recognized recently (30). EQ-5D-3L questionnaire is widely applied to evaluate HRQoL and has been validated in patients with MI (17, 30). In this study, we hypothesize that the EQ-5D-3L index scores will be increased after moderate-intensity CR treatment in participants with LVA formation after anterior MI. This study will also shed light on the change of cardiac function, the occurrence of MACCE and levels of sST2 in post-MI patients with LVA. This study will therefore contribute to the existing knowledge on the prognostic impact of CR in patients with LVA after anterior MI.

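### The plan names only unadjusted tests for continuous outcomes and fixes no primary contrast for peak VO2, although baseline CPET is scheduled for everyone; a prespecified ANCOVA would settle the contrast and gain precision at no cost

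*Protocol article*

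**What the plan says.** The Data analysis section has one general rule for continuous variables: "Normally distributed continuous variables are expressed as mean ± SD and performed with paired or unpaired" t-tests. Non-normal variables go to the Wilcoxon signed-rank or Mann-Whitney test. The section does not mention peak VO2, does not say which of the four tests is the primary comparison, and names no model with a covariate.

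The primary outcome is worded in two ways.
- **Post-programme value.** Outcomes: "The primary outcome of this study is peak VO_2_ after CR program". The Trial design paragraph of the Abstract agrees.
- **Before-after change.** The Background refers to the change in peak VO2, which "will be measured as one of the primary outcomes before and after CR program in patients with LVA post-MI". The Discussion states: "The GRACE study directly targets the change of peak VO_2_ before and after personalized moderate intensity CR program". It then hypothesises that training will raise peak VO2 in these participants and names no comparator.

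Baseline data are planned. Under Study design, CPET "will be performed before and after intervention", and Table 1 marks CPET at baseline and after the programme. The Sample size section uses a calculation for two independent means, with no baseline covariate or correlation.

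**The concern.** Baseline peak VO2 will be measured in everyone and can be expected to correlate with the later value. A comparison of post-programme values that ignores it carries avoidable variance.

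The contrast is also open. With a paired test, an unpaired test and two definitions of the outcome in the same article, three results could be put forward as the primary one: the change within the CR arm, the between-arm difference in change, and the between-arm difference in post-programme values. Each has a parametric and a rank version. A within-arm test does not use the control group, so recovery over time or familiarity with the exercise test could make it significant without any effect of training.

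**Working it through.** **Inputs (Sample size section).** Baseline: control 18.2 (SD 4.4), CR 18.8 (SD 3.7). After the programme: control 17.1 (SD 4.6), CR 21.6 (SD 4.5). Two-sided alpha 0.05, power 90%, 37 per arm, 50 per arm after 25% dropout. The pre-post correlation r is not given, so a range is assumed.

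**1. The plan's own figure.** The dropout step reproduces: 37 / 0.75 = 49.3, rounded up to 50. The 37 does not follow from the post-programme values: a difference of 4.5 with SD √((4.6² + 4.5²)/2) = 4.55 needs 22 per arm by the normal approximation, or 23 by the t-test. A value of 37 does appear for CR after the programme against control at baseline (difference 3.4, SD 4.45). It also appears for a difference in change of 3.9 with r about 0.3 (37 by the normal approximation, 38 by the t-test). That is a separate matter. Here it shows only that the sample size does not reveal whether post values or changes are to be compared.

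**2. Effect by contrast, same planning data.**
- Post values between arms: 21.6 − 17.1 = 4.5
- Change between arms: (21.6 − 18.8) − (17.1 − 18.2) = 2.8 + 1.1 = 3.9
- Change within the CR arm: 2.8

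The first two differ by the baseline gap, 18.8 − 18.2 = 0.6.

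**3. Power without adjustment.** SE = 4.55 × √(2/37) = 1.06. For a true difference of 4.5, the two-sample t-test with 37 per arm has 98.7% power.

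**4. Gain from baseline adjustment.** The residual SD is 4.55 × √(1 − r²). By the noncentral t distribution, the difference detectable with 90% power at 37 per arm is about 3.29 × SE. The degree of freedom spent on the covariate does not change the second decimal by more than 0.01. For change scores, each arm's SD is √(SD_base² + SD_post² − 2r·SD_base·SD_post), combined across arms by root mean square.

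| Assumed r | Variance factor 1 − r² | SE, ANCOVA | Detectable at 90% power | SE, t-test on change |
|---|---|---|---|---|
| unadjusted post values | 1 | 1.06 | 3.48 | – |
| 0.3 | 0.91 | 1.01 | 3.32 | 1.19 |
| 0.5 | 0.75 | 0.92 | 3.01 | 1.01 |
| 0.7 | 0.51 | 0.76 | 2.48 | 0.79 |

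The detectable difference shrinks by about 5%, 13% and 29%. The change-score test is never better than ANCOVA in this range, and at r = 0.3 it is worse than ignoring baseline.

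**5. What a within-arm test would do.** This is an illustration with an assumed drift of 1.0 ml/kg/min unrelated to training. With 37 patients and the CR-arm SDs, the SD of change is √(3.7² + 4.5² − 2r × 3.7 × 4.5) = 4.16 at r = 0.5 and 3.26 at r = 0.7. The paired test would then be significant in about 30% and 44% of trials, with no training effect at all.

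**The case against.** The strongest reply is that the Data analysis section is one general paragraph in a condensed article. It does not name peak VO2 or rule out a covariate, and a statistical analysis plan not shown may specify the model. That is fair, and it limits the point to what the article itself fixes: a list of unadjusted tests with no primary one, beside an outcome defined in two ways. The inconsistent definition is in the text and is not left to another document.

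Four stronger readings are tempting, and the document does not support them.
- **That a within-arm test is the planned primary analysis.** It is not stated. The trial is randomised 1:1, the sample size is for two independent means, and the Outcomes section gives a post-programme value, all of which point to a between-arm comparison. Listing a paired test is routine. The within-arm claim is a risk that the wording leaves open, no more.
- **That the unadjusted test is biased by chance baseline imbalance.** It is not. Under randomisation that imbalance is already inside the unadjusted standard error, and the type I error is correct. The 0.6 gap in the planning study belongs to another trial.
- **That the trial is underpowered without adjustment.** On the cited post-programme figures it has about 99% power with 37 per arm.
- **That normality decides between paired and unpaired tests.** It decides between t-tests and rank tests. Pairing depends on whether the comparison is within or between arms.

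It is also true that the gain depends on an assumed correlation and is small at 0.3, and that a t-test on change would recover most of it at high correlation. But the article does not commit to that test either.

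**Conclusion.** The point holds as a recommended improvement, not as a threat to validity. The article names only unadjusted tests, leaves the primary comparison for peak VO2 open, and defines that outcome both as a post value and as a change. On its own planning data this choice moves the effect between 4.5 and 3.9 ml/kg/min.

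Adjusting for a baseline that is already scheduled lowers the difference detectable with 90% power from 3.48 to between 3.32 and 2.48 ml/kg/min. This assumes 37 evaluable patients per arm, a common SD of 4.55, a linear relation to baseline and a correlation of 0.3 to 0.7. The gain matters most if the true effect in patients with aneurysm is smaller than the cited 4.5.

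**What to change.** In the Data analysis section, state one primary analysis: an ANCOVA of post-programme peak VO2 on arm, with baseline peak VO2 as covariate, reporting the adjusted between-arm difference with its 95% confidence interval. State that this analysis will not be switched on the result of a normality check. Report paired within-arm results as description only.

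In the Background and Discussion, align the wording with the Outcomes section and state the hypothesis as a difference between the CR and control arms. With baseline as covariate, the estimated arm effect is the same whether the post value or the change is the dependent variable, so this also removes the conflict between 4.5-type and 3.9-type contrasts.

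The cost is analysis wording only. No visit, measurement or patient is added, the model can be run in the SPSS software already named, and the recruitment target need not change on this account.

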### Sample size

The sample size of this study was generated using PASS (Power Analysis and Sample Size) version 15.0 statistical software (UT, USA) (20). Sample size calculations were conducted for two independent means. The parameters include predicted value of peak VO_2_, significance level (α) and power (1 – β). Based on previous study, the peak VO_2_ at baseline was 18.2 ± 4.4 ml/kg/min in control group and 18.8 ± 3.7 ml/kg/min in moderate-intensity CR group, the peak VO_2_ after exercise program was 17.1 ± 4.6 ml/kg/min in control group and 21.6 ± 4.5 ml/kg/min in moderate-intensity CR group (21). To achieve 90% power and a 2-sided critical threshold of 0.05, the sample size required in each arm is 37 subjects. Allowing for a drop-off rate of 25%, the recruitment goal is 50 subjects per arm (*n* = 100).

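### The 1-year EQ-5D-3L and echocardiographic comparisons rest on single-visit tests that neither adjust for baseline nor use the post-programme value of a participant with no 1-year value

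*Protocol article*

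**What the plan says.** The protocol article's Outcomes section lists as secondary "HRQoL at after CR program and 1-year quantified with the EQ-5D-3L index scores", and also "the change of cardiac function after CR program and 1-year". Table 1 marks EQ-5D-3L and echocardiography at baseline, after the CR programme and at 12 months. CPET and D-SPECT are marked only at the first two visits.

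The Data analysis section gives one rule for all continuous variables. If normal, they are "performed with paired or unpaired Student's *t*-test"; if not, "determined by Wilcoxon signed-rank test or Mann-Whitney *U* test". It names no repeated-measures or baseline-adjusted model. The same section promises both intention-to-treat and per-protocol analyses.

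The Sample size section requires 37 per arm for peak VO2 and raises this to 50 ("Allowing for a drop-off rate of 25", in per cent).

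**The concern.** Each named test uses one value, or one pair of values, per participant. The paired tests compare visits within an arm and are not the randomised comparison. That leaves the unpaired t-test or Mann-Whitney test to compare arms at 1 year. Applied to 1-year values, these tests ignore two things already collected:

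- **Baseline.** It is likely to predict the 1-year value, so adjusting for it sharpens the comparison.
- **The post-programme value.** A participant seen after the programme but not at 12 months has a measured result that could inform the 1-year estimate. A single-visit test cannot use it.

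The stake is the trial's evidence on whether any benefit for quality of life and cardiac function lasts to 1 year. Precision is given up. If people who did badly after the programme are the ones who leave, and more so in one arm, the raw 1-year comparison is shifted. Outcome assessors are blinded, but participants know whether they are exercising, so loss could differ by arm.

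**Working it through.** **Inputs from the article.** 37 evaluable and 50 recruited per arm; 25% drop-off; two follow-up visits for EQ-5D-3L and echocardiography.

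**Inputs assumed, because the article gives none.** The correlations between visits, when participants leave and why, and a true 1-year difference of 0.5 SD in the simulation.

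**Step 1: the plan's own inflation.** 37 / (1 − 0.25) = 49.3, rounded up to 50 per arm. This reproduces.

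**Step 2: precision under random loss.** Simulation with 4,000 runs per setting, 50 per arm, equal correlation between all three visits, and 25% missing at random at 1 year only. Standard errors are in SD units:

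| Correlation | Unpaired t-test | Completers, adjusted for baseline (ANCOVA) | Longitudinal model (baseline and post-programme value) | Reduction, model v t-test | Reduction, model v ANCOVA |
|---|---|---|---|---|---|
| 0.3 | 0.231 | 0.223 | 0.222 | 4% | 0.4% |
| 0.5 | 0.228 | 0.201 | 0.199 | 13% | 1.0% |
| 0.7 | 0.230 | 0.166 | 0.163 | 29% | 1.8% |

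For the assumed 0.5 SD difference, power rises from about 58–59% to 61%, 71% and 87%. The last column shows that baseline adjustment supplies nearly all of the gain.

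**Step 3: bias when loss depends on the post-programme value.** Same simulation, true difference 0.50 SD. Mean estimates at correlations 0.3 / 0.5 / 0.7:

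| Loss mechanism | t-test on 1-year values | t-test on change from baseline | Longitudinal model |
|---|---|---|---|
| Same rule in both arms | 0.48 / 0.47 / 0.45 | 0.50 / 0.49 / 0.50 | 0.50 / 0.50 / 0.50 |
| Control arm only (CR arm random) | 0.44 / 0.39 / 0.35 | 0.51 / 0.50 / 0.50 | 0.51 / 0.50 / 0.50 |

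The change-score test does well here because all correlations were set equal: the covariance of (1-year − baseline) with the post-programme value is then ρ − ρ = 0 in SD units. Unequal correlations would break this.

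**Step 4: dependence on the timing of loss.** Let m per arm be seen after the programme and 37 at 1 year, with correlation ρ between these visits. Ignoring baseline, the variance of the 1-year arm mean when the earlier visit is used, relative to completers only, is 1 − ρ²(1 − 37/m), and the effective number is 37 divided by that ratio. Suppose CR-arm drop-outs were 1 SD below completers after the programme and controls left at random. The raw 1-year difference is then biased towards CR by ρ × 1 SD × (m − 37)/m.

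| Seen after programme, then at 1 year | Variance ratio, ρ = 0.5 to 0.8 | Effective n per arm | Bias (SD) |
|---|---|---|---|
| 37, then 37 | 1.00 | 37 | 0 |
| 40, then 37 | 0.98 to 0.95 | 37.7 to 38.9 | 0.04 to 0.06 |
| 50, then 37 | 0.935 to 0.834 | 39.6 to 44.4 | 0.13 to 0.21 |

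The zero in the first row is only the bias that the post-programme value could remove. Participants lost before that visit have no such value under either method.

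**The case against.** The strongest reply is that a two-sample test at a stated visit is a valid randomised comparison, and that the handling of missing values is properly left to a statistical analysis plan that is not shown. Several parts of this stand.

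- **A reader might infer that the plan discards everyone without a 1-year value.** No sentence says so. It follows only if the named tests are run without imputation, and intention-to-treat analysis is promised. The exclusion criterion covering participants who drop out points towards a completers analysis, but that is a separate matter which changing the test would not cure.
- **A reader might infer that the post-programme values go unused.** They do not: they are secondary outcomes and are analysed at their own visit. They are only not borrowed for the 1-year estimate.
- **A reader might take 0.13–0.21 SD as the expected bias.** The 25% allowance protects the peak VO2 comparison, and CPET ends at the post-programme visit. Placing all 13 losses per arm after that visit is the split most favourable to a mixed model. The article gives no figure for later loss and no support for a one-arm mechanism.
- **Cardiac function is worded as a change.** An unpaired t-test on change fits that wording and was nearly unbiased in the simulated settings. It is still less precise than baseline adjustment: its standard error was 0.276, 0.232 and 0.179 at correlations 0.3, 0.5 and 0.7.

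What remains is that the article itself chose the tests. Imputation could be added around them, but as named they do not adjust for baseline by regression and cannot draw on an earlier visit.

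**Conclusion.** The point holds as a recommendation to use a better method for secondary outcomes. The named tests do not match a design that measures EQ-5D-3L and echocardiography three times and expects losses.

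The firmer gain is precision, which comes almost entirely from baseline adjustment and grows with the correlation between visits. The second follow-up visit adds little precision under random loss; its value is protection against bias, and the size of that depends on assumptions the article cannot settle. It could be nothing if losses come before the post-programme visit, and reaches the top of the range in Step 4 only if all losses come after it and follow the assumed one-arm pattern.

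Nothing here shows that the 1-year results will be biased. A reader might extend the point to the primary outcome, but peak VO2 has a single follow-up CPET, so there is no second follow-up value to use.

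**What to change.** In the Data analysis section, for the EQ-5D-3L index and each echocardiographic indicator, specify one linear mixed model fitted to all randomised participants with at least one follow-up value. Include arm, visit, arm-by-visit, baseline and baseline-by-visit, with an unstructured covariance over the two follow-up visits. Report the between-arm difference with its 95% confidence interval after the programme and at 1 year. Keep the t-tests or rank tests as support.

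Report deaths before 1 year by arm alongside these results, because the model otherwise implicitly assigns quality-of-life and cardiac-function values to participants who have died.

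The cost is a sentence or two in the plan and slightly more analysis work. No extra visits or data are needed, and the stated SPSS package fits such models. The model assumes that loss depends only on observed values. This is weaker than what a completers-only comparison of 1-year values needs, but it is still an assumption, and the model does not recover participants with no follow-up value at all.

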**Trial design:**

The GRACE study is a single-center, single-blind, prospective, randomized controlled clinical trial in China. 100 subjects aged 18–75 years with LVA formation after anterior MI will be recruited and randomized 1:1 to the CR or control group. Both groups will receive standard drug treatment and routine health education according to the guidelines. Participants in the CR group will additionally receive tailored CR programs delivered over a period of 36 sessions. These participants will then be followed up for 1-year. The primary outcome is peak oxygen uptake measured by cardiopulmonary exercise testing after CR programs. The secondary outcomes are cardiac function and EuroQol 5-Dimension-3 Level index scores after CR program and 1-year and major adverse cardiac cerebrovascular events, a composite of cardiovascular mortality, non-fatal MI, non-fatal stroke, malignant arrhythmia or hospitalization for heart failure during the follow-up period.

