**Conclusions:**

This single-center, single-blind, prospective, randomized controlled clinical trial will determine whether CR improves physical capacity and clinical outcomes in patients with LVA formation after anterior MI.

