After tailored and progressive in-hospital training sessions for 3 times, participants will continue to perform physician-supervised home-based exercises 5 sessions per week and 30 min per session, scheduled for 36 sessions. The home-based exercise consists of moderate intensity aerobic exercise at a target HR reserve (HRR). Participants will be required to perform outdoor walking exercise at an intensity of 50% of HRR based on the results of CPET monitored by a pulse-watch. The required exercise intensity will be measured subjectively using a Borg score of 11–13. Details about the benefits of home-based CR program in optimizing cardiovascular health will be provided to the participants. A booklet is encouraged to use to record exercise time, HR and any discomfort during exercise. Participants will receive telephonic feedback on training frequency, duration and intensity from the physical therapist per week during the 36 sessions. The physical therapist will give feedback on training parameters measured during the preceding week and discuss the progress with respect to the personal training goals. Then, the participants will be advised to continue their training with the HR monitor. Participants will receive in-hospital training guidance every 2 weeks. A long-term home-based exercise plan will be made by the physical therapist after the CR program. Subjects will be followed up for 12 months.

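### The Kaplan-Meier analysis is assigned to mean survival time, which is not the 1-year MACCE outcome and depends on how long each arm happens to be followed

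*Protocol article*

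**What the plan says.** The Data analysis section names one time-to-event method and one summary from it: "Kaplan-Meier analysis are used to calculate the mean survival time of the patients". It does not name the event, a time horizon or the MACCE composite. The same section covers yes/no outcomes separately: "Categorical variables are presented as frequency and percentage (*N*, %) and evaluated by χ^2^ test or Fisher's exact test as appropriate".

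Under Outcomes, the clinical secondary outcome is "the occurrence of MACCE at 1-year". The abstract defines MACCE as "a composite of cardiovascular mortality, non-fatal MI, non-fatal stroke, malignant arrhythmia or hospitalization for heart failure".

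The start of follow-up is worded in two ways. Study design says "All of the participants will be followed up for 1-year". The abstract first describes the 36 sessions given to the CR group and then says "These participants will then be followed up for 1-year". The Intervention section sets the home program at "physician-supervised home-based exercises 5 sessions per week and 30 min per session, scheduled for 36 sessions". Table 1 has a single 12-month column for everyone.

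The abstract's conclusion is that the trial "will determine whether CR improves physical capacity and clinical outcomes in patients with LVA formation after anterior MI". The Sample size section is based only on peak VO2.

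**The concern.** Two things do not fit together.

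First, the quantity. Survival time, read literally, is time to death. The outcome is time to, or occurrence of, a composite in which only cardiovascular mortality is fatal. If MACCE-free survival was intended, the sentence does not say so.

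Second, the summary. A mean requires the whole event-time distribution. When the curve is still well above zero at the last observation, the mean is not identified, and the Kaplan-Meier mean becomes a restricted mean whose upper limit is the largest observed time in that arm. That limit is set by visit timing and the choice of time origin, not by treatment. Two arms with the same risk can then show different means, and the gap may be read as a treatment effect.

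At stake is the interpretation of one secondary result. The primary outcome, the sample size and the data collected are unaffected.

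**Working it through.** The article gives no MACCE rate and no design figure for MACCE, so there is no stated number to reproduce. The rates below are assumptions and a range is shown.

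**Inputs from the article**
- Follow-up: 1 year (Study design; Table 1).
- Home program: 36 sessions at 5 per week (Intervention), so 36/5 = 7.2 weeks. In months, 7.2 × 7/30.44 = 1.66.
- Recruitment: 50 per arm (Sample size).

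**Assumptions**
- Exponential time to first MACCE with 12-month risk p, so λ = −ln(1 − p)/12 per month.
- Time counted from randomisation.

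**Restricted mean up to time τ:** RM(τ) = (1 − e^(−λτ))/λ.

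For p = 0.20, λ = 0.2231/12 = 0.018595:
- RM(12) = 0.20/0.018595 = 10.76 months.
- Hazard halved: RM(12) = 11.35, a true effect of 0.60 months.
- Same hazard, horizon 13 months: RM(13) = 11.55, a gap of 0.79 with no treatment effect.
- Same hazard, horizon 13.66 months (12 months plus 7.2 weeks): RM(13.66) = 12.06, a gap of 1.30 with no treatment effect.

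Across assumed 12-month risks:

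| p | RM(12) | True effect of halving the hazard | Spurious gap, horizon 1 month longer | Spurious gap, horizon 7.2 weeks longer |
|---|---|---|---|---|
| 5% | 11.70 | 0.15 | 0.95 | 1.57 |
| 10% | 11.39 | 0.30 | 0.90 | 1.48 |
| 20% | 10.76 | 0.60 | 0.79 | 1.30 |
| 30% | 10.09 | 0.90 | 0.69 | 1.13 |

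A 7.2-week difference in horizon outweighs a halved hazard at every rate shown. A one-month difference does so up to 20% but not at 30%.

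**Simulation check.** With 50 per arm, equal hazards and p = 0.20, censoring was uniform from 11.5 months up to 14 months in one arm and up to 12.5 in the other. The mean gap was 1.15 months when each arm ran to its own last time. It was 0.00 when both were cut at a common 11.5 months. The artefact comes entirely from the missing common horizon.

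**Precision, for the abstract's wording.** If both arms have 20% MACCE, the 95% CI half-width for a difference with 50 per arm is 1.96 × √(2 × 0.20 × 0.80/50) = 0.157, about 16 percentage points. At 10% it is 12 points and at 30% it is 18.

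**The case against.** The strongest reply is that MACCE at 1 year is a yes/no variable at a fixed time, and the plan already assigns such variables to a chi-square or Fisher test, which compares the arms directly. That stands. A reader might infer that MACCE is left without a usable analysis; the article does not support that.

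The second reply is that everyone is to be followed for a year with one common 12-month visit, and no section states different follow-up by arm. That also stands: if both arms are cut at exactly 12 months from randomisation, the horizon artefact vanishes. It would be wrong to illustrate the problem with one arm ending early, say at 11 months. That would require every patient in the arm to have had an event or been lost by then. The realistic route is a longer horizon in one arm, through late visits or a year counted from the end of the CR program. The abstract's wording allows the latter reading but does not establish it.

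Other stronger readings also fail:
- **Drop-off.** The 25% in the Sample size section inflates a calculation for peak VO2 after the program. It is not a stated loss rate for 1-year events, and how lost patients count in the yes/no analysis may be set out in a document not shown.
- **Missing detail.** A log-rank or Cox comparison and competing-risk handling may likewise be specified elsewhere, so their absence is not held against the article.
- **Power.** A secondary outcome need not be powered, and any power figure for MACCE would rest wholly on assumed rates. The Discussion is also more modest about MACCE than the abstract.

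What the replies do not reach is the sentence itself. It names a summary that is neither the stated outcome nor estimable with this follow-up, and a fuller plan elsewhere would not make it correct.

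**Conclusion.** The point holds, confined to the Kaplan-Meier sentence, and is minor to moderate. The mismatch with the MACCE outcome and the non-estimability of the mean need no event-rate assumption beyond many patients being event-free at the end of follow-up.

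The size of the distortion is conditional. It is nil with a common 12-month cut-off. It is about 1.1 to 1.6 months, for assumed 12-month risks of 30% down to 5% and an exponential hazard, if one arm's horizon runs 7.2 weeks longer. The article does not show that this will happen; it fixes no horizon in that sentence to prevent it.

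The abstract's claim to determine clinical outcomes is a secondary wording matter. It stems from sizing the trial on peak VO2 alone, not from the Kaplan-Meier sentence.

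**What to change.** Replace the Kaplan-Meier sentence with wording such as: *Time from randomisation to first MACCE will be summarised by Kaplan-Meier; the MACCE-free probability at 12 months will be reported for each arm, with the between-arm difference and its 95% confidence interval.* If a mean is preferred, use restricted mean MACCE-free time to the same 12 months in both arms, with the difference and 95% CI.

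Use one wording for the start of follow-up in the abstract and Study design, applied to both arms.

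In the abstract's conclusion, keep the firm claim for physical capacity and say that the trial will estimate or explore the effect on clinical outcomes.

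The cost is a few sentences and a more modest claim. The data, visits and sample size do not change.
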